### Safety assessments

Spontaneously reported adverse events will be recorded throughout the study. Vital signs will be monitored at every visit. Laboratory investigations including haematology, blood chemistry and urinalysis will be performed at Day 0 and Day 28, and repeated on a need basis. For all adverse events the intensity, relation to test drug, and actions taken will be recorded. All adverse events including reports of skin irritation will be followed until resolution of the event occurs.

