## Methods/design

### Study design

This is a prospective, five-center, parallel-group, randomized controlled efficacy and safety study of individually integrated TCM approach in subjects with knee OA. After giving informed written consent, patients undergo a treatment period of four weeks. Ethics approval was received from Chinese Cochrane Center with the NO:ChiCTRCTET2008-9.

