### Intervention

On Day 0 (Visit 1), patients will begin treatment with either herbal drug, herbal patch, acupuncture, Tuina, or integrative approach. On Day 14, patients will return for an interim visit (Visit 2). On Day 28, the final visit will take place (Visit 3). Thus, the duration of treatment is 4 weeks.

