### Tuina

The manipulation will be performed according to established standard operation procedure (SOP) (Table 2).

**Table 2 T2:** Tuina therapy for knee OA

Sequence number	Tuina manipulation
1	The therapist using grasping or rolling applies to the back of the thigh and the crus for 2 minutes.
2	Pushing, kneading or pushing with one-finger meditation on popliteal fossa for 2 minutes.
3	Rolling applies to tensor fascia lata, quadriceps and adductors in the limb for 3 minutes.
4	Rubbing, kneading or pushing with one-finger meditation applies to the Dubi(ST35), Neixiyan(EX-LE5), Ashi points, and each acupoint is about 40 seconds.
5	Gently Pushing the patella to the upward, downward, inward and outward directions for several times, then to the extreme limit of patella and maintaining for 2 and 3 seconds. Repeat 3 times.
6	Pulling the knee. The assistant helps fix the distal thigh, and the therapist uses hands to hold the distal leg and pull for 2 seconds. Repeat 5 times.
7	Passive flexion and extension, adduction and abduction of hip and knee joint to the utmost degree that patient can stand. Repeat 3 times.

Description: The power of tuina manipulation requires evenly and gently application to the degree that patients feel comfort and tolerance. In operations 1 and 2, the patient remains in the prone position. In operations 3 through 7, the patient assumes the supine position.

Dose: about 20 minutes each time and 2 times per week.

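### Volunteered reports are the only stated source of symptomatic adverse events, arms differ in therapist contact, and the causality item is worded for a drug that two arms do not receive

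*Protocol article*

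**What the plan says.** The Study design section calls the trial a "randomized controlled efficacy and safety study". Its provisions for adverse events are in Safety assessments:

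- Collection: "Spontaneously reported adverse events will be recorded throughout the study". No scheduled enquiry or checklist is described.
- Scheduled measurements in every arm: "Vital signs will be monitored at every visit", and "Laboratory investigations including haematology, blood chemistry and urinalysis will be performed at Day 0 and Day 28, and repeated on a need basis".
- Attributes of each event: "For all adverse events the intensity, relation to test drug, and actions taken will be recorded".
- Follow-up: "All adverse events including reports of skin irritation will be followed until resolution of the event occurs".

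The arms are listed under Intervention: "patients will begin treatment with either herbal drug, herbal patch, acupuncture, Tuina, or integrative approach". All arms share Day 0, Day 14 and Day 28. The Tuina section (Table 2) adds sessions of "about 20 minutes each time and 2 times per week". The Acupuncture section gives no frequency and refers to cited procedures. Table 3 lets WOMAC item scores decide which components an integrated-arm patient receives. The Quality assurance section leaves patients, investigators and therapists unblinded. Blinded assessors cover the primary and secondary endpoints, and every endpoint listed under Endpoints is an efficacy measure.

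**The concern.** There are two separate points.

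**Ascertainment.** A volunteered report needs an occasion and someone to tell. If one arm meets study staff more often than another, the same true event rate can produce different recorded rates. Unblinded patients and staff may also expect different harms from different treatments. The patch diary is described as serving compliance, so it is not a stated counterweight. At stake is the safety half of an efficacy and safety trial: an arm could look better or worse tolerated because of how its events came to light. Bruising, soreness after manipulation and stomach upset are complaints that vital signs and laboratory tests are not designed to detect.

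**Attribution.** The causality item is required for every event in every arm but refers to a test drug. Two arms have none. A third can combine up to four components, and a single judgement against one unnamed drug does not say which component is suspected.

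**Working it through.** The document gives no adverse-event rate, reporting probability or safety power, so there is no figure of its own to reproduce. Three things can be checked.

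**1. Contacts over the 4 weeks**

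| Arm | Contacts after baseline, from the document |
|---|---|
| Capsule alone, patch alone | Day 14 and Day 28: 2 |
| Tuina alone | 2 sessions/week × 4 weeks = 8 sessions, plus any visit not on a session day: 8 to 10 |
| Acupuncture alone | 2 visits plus an unstated number of sessions |
| Integrated | 2 visits plus 0 or more sessions, depending on WOMAC items |

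The Tuina ratio to capsule or patch is 8/2 = 4 if two sessions fall on visit days, and 10/2 = 5 if none do. If the first session is on Day 0, each count drops by one: 7/2 = 3.5 to 9/2 = 4.5. In the integrated arm, Table 3 adds Tuina when any of 17 function items reaches 40 mm and acupuncture when any of 5 pain items does. Patients below both thresholds receive capsule, with or without patch, and no therapist sessions.

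**2. What unequal reporting could do (illustration on assumed rates)**

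Let the true risk *p* be equal in two arms, and let a fraction *a* of events be reported in the low-contact arm and *b* in the high-contact arm. The recorded risks are *pa* and *pb*, so the apparent risk ratio is *b/a* whatever *p* is. With *n* = 100 per arm (500/5, assuming equal allocation, which is not stated), the chance that a two-sided 5% test declares an excess in the high-contact arm is approximately

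Φ{[*p*(*b* − *a*) − 1.96·SE₀] / SE₁},

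where SE₀ = √[2·m(1 − m)/*n*] with m = *p*(*a* + *b*)/2, and SE₁ = √{[*pa*(1 − *pa*) + *pb*(1 − *pb*)]/*n*}.

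Worked case, *p* = 0.10, *a* = 0.5, *b* = 0.8: the recorded risks are 0.05 and 0.08, SE₀ = 0.0349 and SE₁ = 0.0348. Then (0.03 − 0.0683)/0.0348 = −1.10, which gives 0.135.

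| Reporting, low vs high contact | Apparent risk ratio | *p* = 10% | *p* = 20% | *p* = 30% |
|---|---|---|---|---|
| 50% vs 65% | 1.3 | 7% | 10% | 13% |
| 50% vs 80% | 1.6 | 14% | 24% | 36% |
| 40% vs 90% | 2.25 | 30% | 56% | 77% |

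With equal reporting the apparent ratio is 1 and the chance in this direction is the nominal 2.5%. The reporting fractions are assumptions. The table shows how the result depends on them and does not estimate this trial.

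**3. The causality item against the arms**

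| Arm | Does the term test drug have a referent? |
|---|---|
| Capsule alone | Yes |
| Patch alone | Yes, the herbal patch |
| Acupuncture alone | No |
| Tuina alone | No |
| Integrated | Not unique: capsule, with patch, acupuncture and Tuina as scores dictate |

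The wording therefore fails in 2 of 5 arms and is unspecific in a third.

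**The case against.** The strongest case on the other side has four parts.

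- **The text does not say that only volunteered events are captured.** Vital signs and laboratory tests are systematic and identical in all arms. This stands, and it limits the point to symptomatic events.
- **This is a condensed article.** A visit question or a component-level causality field may exist in the full protocol or case report form. That is possible. But the article states a collection method and a causality item, and the point rests on those statements rather than on an omission.
- **Contact is not reporting.** Investigators, therapists and assessors are different people, nothing says therapists record adverse events, and reports are accepted throughout the study. The contact ratio therefore cannot be read as a reporting ratio. This stands.
- **No between-arm test of adverse events is planned in the article**, and the stated hypothesis concerns efficacy. This also stands. The false-positive figures describe a comparison that a reader of the results might make, not one the plan specifies.

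Two stronger readings are tempting, and the document supports neither. A reader might infer that the hands-on arms, including the integrated arm, are bound to look less safe whatever the true rates. Size and direction depend on reporting rates that are not given; some integrated-arm patients have no therapist sessions, and the acupuncture frequency is unknown. A reader might also infer that acupuncture or Tuina harms cannot be classified, or would be logged as unrelated. These events are still recorded with intensity, actions taken and follow-up to resolution. Only the causality item lacks a suitable referent, and how staff would complete it is not stated.

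**Conclusion.** The point holds in limited form, as a minor improvement. The stated route for symptomatic adverse events leaves room for unequal ascertainment in an open-label trial whose arms differ in contact. The documented difference is Tuina against capsule or patch: about 8 added therapist sessions beside 2 post-baseline visits. It cannot be extended to acupuncture, and in the integrated arm it varies by patient. Whether adverse-event counts would in fact be distorted, by how much and in which direction, cannot be determined from the document. The mismatch in the causality wording can be read directly from the text and needs no assumption. Neither point bears on the WOMAC analysis or the sample size.

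**What to change.** 1. At Visit 2 and Visit 3, in all five arms, ask one standard, non-leading question about adverse events, worded identically.
2. Report all adverse events by arm, including every serious event and every volunteered event. Show the events elicited at the two common visits separately, as the like-for-like comparison between arms. Restricting the comparison to elicited events and merely listing the rest would be a mistake, because a serious event reported between visits could then drop out of it.
3. Replace the relation to test drug with the relation to study intervention, recorded by component: capsule, patch, acupuncture, Tuina. In the integrated arm this records the investigator's judgement. It will not settle attribution when components are given together, but it can be read against the treatment records already kept.

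The cost is one question at existing visits, one extra case report form field, and more minor events on record. No treatment or visit changes.

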### Sample size

Sample size calculations were based on published data [5,14,16]. The mean differences in WOMAC scores before and after treatment with the integrative TCM approach, counter osteophytes capsule, Fufang Zijin patch, acupuncture and Tuina are 11 (SD = 5), 12 (SD = 6), 9.34 (SD = 4.09), 10.17 (SD = 3.85) and 8.89 (SD = 4.32), respectively. Using these data we estimated that 420 patients would be sufficient to give 0.8 power at 0.05 alpha level. Allowing for dropout, we plan to enroll 500 patients.

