Tuina is a very important component of TCM together with acupuncture and herbal medicines. Tuina, called 'An Mo' or medical massage in ancient times, usually refers to the doctor using their hands to manipulate the patient's body surface by means of various forms of tuina maneuvers such as pushing, kneading, rolling, wrenching, and flicking-plucking to relax and dredge the meridians and promote Qi flowing and blood circulating. Tuina is considered a natural treatment and manual therapy. It is distinct from chiropractic, osteopathic and mobilization because Tuina is used under the guidance of the basic theory of TCM. Among alternative care consumers with OA, the most commonly used treatment was massage therapy (57%) [6]. Some reports documente similar massage therapy as efficacious in the treatment of OA of the knee [7], but a systematic review of recent trials failed to confirm its efficacy [8].

In many Asian countries and increasing in western countries, acupuncture is a very popular treatment for OA. Systematic reviews and RCTs support the effectiveness of acupuncture for OA pain [9,10].

Optimal management of OA calls for an individual approach based on different constitutions of human body [11]. The individually integrated TCM approach in this study has been formed during 15 years of clinical experience in Shuguang hospital affiliated to Shanghai university of TCM. The approach consists of a basic treatment of orally administered Chinese herbal drugs and varying use of Tuina, acupuncture and herbal patch, all based on the severity of the patient symptoms.

We therefore initiated this study to compare the efficacy of an individually integrated TCM approach, Chinese herb counter osteophytes capsule, Fufang Zijin patch, acupuncture and Tuina in the short-term, symptomatic treatment of OA of the knee. We hypothesized that the integrated TCM approach is more effective than the four treatments, oral medication, topical patch, acupuncture or Tuina, when used alone.

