### Sensitivity analysis

In this analysis missing data for patients prematurely discontinuing from the trial (or for patients for other reasons not included in the full analysis set) are generated by random draw from the completer patient data, then adjusted as described below. The analysis is described for a situation where treatment A is statistically significantly superior to treatment B by the primary efficacy analysis. The treatment effect is the difference of the WOMAC change in the treatment A and the WOMAC change in treatment B. Call this treatment effect difference D. Four scenarios are investigated, corresponding to the loss of 25%, 50%, 75%, and 100% of the treatment effect difference. Patients that prematurely discontinued from treatment A will have their WOMAC change values determined by random draw (with replacement) from the treatment A completers, then these values are adjusted downward by 1/8*D, 2/8*D, 3/8*D, then 4/8*D, for the 1^st^, 2^nd^, 3^rd^, and 4^th ^scenario, respectively. Treatment B dropouts will have their random draw values adjusted upward sequentially by the same factors (1/8*D, 2/8*D, 3/8*D, then 4/8*D). The four scenarios, therefore, are:

#1-Assuming loss of 25% of the treatment effect; this is the least adverse scenario.

#2-Assuming loss of 50% of the treatment effect seen in completers.

#3-Assuming loss of 75% of the treatment effect seen in completers.

#4-Assuming loss of 100% of the treatment effect; this is the most adverse scenario.

Because the analysis involves stochastic variables, it will be repeated 100 times in order to better estimate the means and approximate 95% confidence intervals.

The following treatment comparisons will be performed based on the repeated measures mixed model and sensitivity analysis:i) Comparison at each of Days 0, 14, and 28;ii) Comparison of the Day 14 and 28 averages, using the time-averaged Day 14 and 28 scores estimated within the model framework;iii) Comparison of the average over all post-treatment days, using the time-averaged Day 14 and 28 scores estimated within the model framework;iv)All statistical tests will be two-sided. The primary endpoint and key secondary endpoints will be tested.

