## Discussion

The biggest limitation of this study is the lack of placebo control. It should be noted that the aim of this trial is not to estimate the efficacy of treatments used, but to demonstrate that individually integrated TCM approach is superior to individual component alone. This aim arises from clinical experience. The components of these treatments have been used for centuries. TCM has over 2000 years' application in China, usually as "one method applied in a whole course of treatment". However, even though the individual approach, based on different features of OA, is recommended, there is no evidence that it is superior to a treatment component used alone.

In an OA trial, a statistically significant result might be due to the dropout pattern rather than a true treatment effect, so we are attempting to collect data at the time of discontinuation to enable better comparisons of those completing versus those discontinuing. Additionally, we are conducting a formal sensitivity analysis using imputed data for discontinued patients to determine whether a positive result remains positive in scenarios where part or all of the treatment effect difference seen in the completers is lost in the dropout patients. To our knowledge, this is the first trial in a chronic symptomatic disorder to explicitly specify this type of sensitivity analysis to address trial dropouts.

Our results will be conditional on the population recruited, and the patients we recruited, requiring pain intensity of 20 mm or more on visual analogue scales (VAS), may have larger or smaller responses to treatment compared to those without such a restriction. For example, it was recently shown that use of a "flare" to define trial eligibility in OA alters, on average, response to treatment [17]. Another limitation is no double-blinding. Although it is difficult to carry out double-blinding in this design, we blind those clinicians conducting the assessments to decrease possible bias. The study also lacks long-term follow-up and evaluation. However, the duration chosen in the present study is consistent with acute OA flare episodes; and the study is long enough to document a rapid onset of a treatment modality and its efficacy sustained for 4 weeks. The protocol has a provision for rescue medication although its use is discouraged.

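### The planning figures put the capsule arm ahead of the integrated arm, so 420 patients cannot give 0.8 power for the trial's hypothesis

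*Protocol article*

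**What the plan says.** The Background section of the protocol article sets the hypothesis: "We hypothesized that the integrated TCM approach is more effective than the four treatments, oral medication, topical patch, acupuncture or Tuina, when used alone". The Discussion repeats the aim as "to demonstrate that individually integrated TCM approach is superior to individual component alone".

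The Sample size section lists the assumed WOMAC changes in a fixed order, with the integrated arm first, the capsule second, then patch, acupuncture and Tuina. The values given are "11 (SD = 5), 12 (SD = 6), 9.34 (SD = 4.09), 10.17 (SD = 3.85) and 8.89 (SD = 4.32), respectively". From these figures the section draws its conclusion: "Using these data we estimated that 420 patients would be sufficient to give 0.8 power at 0.05 alpha level". Enrolment is raised to 500 to allow for dropout.

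The section does not say which comparison or test the 0.8 refers to, and it mentions no division of alpha across comparisons. The end of the Sensitivity analysis section adds: "All statistical tests will be two-sided".

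**The concern.** The inputs contradict the hypothesis that they are meant to power. Read in the printed order, they expect the capsule alone to produce a larger change than the integrated approach, which has the capsule as its base. No sample size gives power for superiority when the assumed effect points the other way; adding patients lowers it. The assumed advantage over acupuncture, 0.83 points, is also small beside SDs of about 4 to 5.

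Reversing the sign convention does not help. If a smaller value were better, the integrated arm would be planned as worse than patch, acupuncture and Tuina.

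What is at stake is how the main result is read. On the plan's own inputs, failing to beat capsule or acupuncture is the expected outcome. With 0.8 power in print, that outcome could be taken as good evidence against the integrated approach, when the trial had little chance of showing otherwise.

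**Working it through.** **Inputs.** Means and SDs are those in the Sample size section. Alpha is 0.05, two-sided. The number per arm is 420 / 5 = 84; equal allocation is assumed because the article gives no ratio.

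**Can 420 be reproduced?** For 0.8 power in one pairwise comparison,

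n per arm = (1.96 + 0.8416)² × (SD₁² + SD₂²) / d² = 7.849 × (SD₁² + SD₂²) / d²

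| Integrated vs | d | SD₁² + SD₂² | n per arm | × 5 arms |
|---|---|---|---|---|
| Capsule | 11 − 12 = −1.00 | 25 + 36 = 61.00 | none (see below) | – |
| Patch | 11 − 9.34 = 1.66 | 25 + 16.73 = 41.73 | 119 | 595 |
| Acupuncture | 11 − 10.17 = 0.83 | 25 + 14.82 = 39.82 | 454 | 2270 |
| Tuina | 11 − 8.89 = 2.11 | 25 + 18.66 = 43.66 | 77 | 385 |

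For capsule the formula returns 479 per arm, but only because squaring d discards its sign. That number would power a finding that the capsule is better.

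A one-way omnibus F test does not give 420 either. The grand mean is 10.28, the squared deviations sum to 6.305 and the mean variance is 22.24, so f = √(6.305 / 5 / 22.24) = 0.238. Power is 0.788 at N = 210, 0.799 at 215 and 0.985 at 420. About 216 patients (220 with equal arms) would be enough for 0.8.

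**Power at 84 per arm.** The standard error is √((SD₁² + SD₂²) / 84). Power in the hypothesised direction is approximately Φ(d/SE − 1.96); the last column uses the noncentral t.

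| Integrated vs | SE | d/SE | Φ(d/SE − 1.96) | Noncentral t |
|---|---|---|---|---|
| Capsule | 0.852 | −1.17 | 0.0009 | 0.0009 |
| Patch | 0.705 | 2.36 | 0.654 | 0.649 |
| Acupuncture | 0.689 | 1.21 | 0.225 | 0.223 |
| Tuina | 0.721 | 2.93 | 0.833 | 0.829 |

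Against capsule, the chance of a significant result in the wrong direction is 0.214.

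**All four together.** Simulating the five arm means (200,000 runs, one shared integrated arm) gives a probability of 0.0007 that the integrated arm beats all four. Leaving the capsule out, it beats the other three with probability about 0.20.

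**If the first two entries were transposed** (integrated 12, SD 6; capsule 11, SD 5):

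| Integrated vs | d | Power, n = 84 |
|---|---|---|
| Capsule | 1.00 | 0.21 |
| Patch | 2.66 | 0.92 |
| Acupuncture | 1.83 | 0.65 |
| Tuina | 3.11 | 0.97 |

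Power for all four jointly is then about 0.20.

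**What 84 per arm can detect** with 80% power, as 2.8016 × SE: 1.93 points vs acupuncture, 1.97 vs patch, 2.02 vs Tuina and 2.39 vs capsule. Joint power for all four, with one common true difference, is about 0.76 at 2.5 points and 0.86 at 2.75, and reaches 0.80 at about 2.6.

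**The case against.** The strongest reply is that the two entries are simply misprinted and that 420 has an ordinary origin. With alpha split over four comparisons (0.05/4, two-sided) and 0.8 power, 12 (SD 6) against 9.34 (SD 4.09) needs 3.339² × 52.73 / 2.66² = 83.1, so 84 per arm and exactly 420. That would be integrated vs patch if the first two entries were switched. Integrated vs Tuina at one-sided 0.05 and 0.9 power also gives 84. So 420 is not inexplicable, and transposition is a live possibility. But neither setting is stated, and the second conflicts with both the stated 0.8 and the two-sided rule. Transposition also leaves capsule and acupuncture short of 0.8 even without any alpha split.

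Second, the planned analysis is a baseline-adjusted repeated-measures model, which may be more precise than raw change scores. This has some force. If adjustment removed 30% of the variance (an illustrative assumption; the article gives no correlation), patch would reach about 0.80 and Tuina 0.94. Acupuncture would reach only 0.30, and the capsule difference would keep its sign.

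Third, nothing in the article says the trial succeeds only if all four comparisons are significant. That is fair: joint power is one reading of the hypothesis. The finding does not need it, since the pairwise figures already fail.

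**Conclusion.** The concern holds. As printed, the inputs contradict the hypothesis, and the stated 0.8 power is met for one of the four comparisons (Tuina, 83%). It is not met for patch (65%), acupuncture (22%) or capsule (0.1%, with a 21% chance of significance the wrong way), nor for all four jointly (about 0.1%). It does not describe the omnibus test either, whose power at 420 is 98.5%.

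These figures assume equal allocation, no alpha split and change-score SDs. An alpha split would lower every pairwise figure. A more precise model could lift the patch comparison to the target, but not acupuncture, and it cannot rescue the capsule comparison. Whether the first two entries were transposed cannot be settled from the article. The stated power fails for the full hypothesis either way, so the paragraph must be corrected.

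**What to change.** Rewrite the Sample size paragraph, keeping N as it is:

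1. Check the integrated and capsule means and SDs against the cited sources, and correct them if they were transposed.
2. Name the comparison or comparisons that the sample size is meant for, with the alpha used for each.
3. Replace the single 0.8 statement with power for each comparison, or with detectable differences. On the printed SDs, 84 evaluable patients per arm give 80% power for true differences of about 1.9 to 2.0 points vs acupuncture, patch and Tuina, and about 2.4 points vs capsule (two-sided 0.05, no alpha split).
4. If success means beating all four, say so, and state that 80% joint power needs a true difference of about 2.6 points in each comparison.

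The cost is one paragraph and a less favourable power statement. No extra patients are needed.
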